## Methods

### Study design

This is a single-arm, prospective, non-randomised, multi-centre study. Patients will be recruited from eleven [11] NHS Trusts throughout the UK (London North West University Healthcare NHS Trust; The Newcastle Upon Tyne Hospitals NHS Foundation Trust; Guy’s and St Thomas’ NHS Foundation Trust; St George’s University Hospitals NHS Foundation Trust; Manchester University NHS Foundation Trust; Birmingham Women’s and Children’s NHS Foundation Trust; Oxford University Hospitals NHS Foundation Trust; Queen Elizabeth Hospital, University Hospitals Birmingham NHS Foundation Trust; Ninewells Hospital, Dundee, NHS Tayside; University Hospitals Bristol NHS Foundation Trust; and University Hospitals Plymouth NHS Trust). Recruitment for this study commenced in September 2021 with active recruitment anticipated to end on 31st March 2023, or when overall accrual reaches *n =* 400.

With eleven participating study sites in the sole intervention arm, we anticipate approximately 2745 Lynch Syndrome patients. Based on published data from England’s national screening programme FIT pilot study [16] of 3933 “prevalent first-time invitees”, 3686 negative tests were identified in a subgroup of patients whose colonoscopy data was unavailable. In addition, 247 FIT positive tests were identified of which 6 individuals were subsequently diagnosed with CRC following colonoscopy. In order to estimate how many cancers may have been missed by the absence of colonoscopies in those 3686 invitees with negative FIT tests, we note that Li et al. [17] estimates that a threshold of 20 μg haemoglobin (Hb)/g of faeces has 82.2% sensitivity to identify CRC, indicating that an estimate of the total number of cancers in the 3933 individuals would be 6/0.822 = 7.3 cancers. Thus, in addition to the 6 CRC cases with FIT positive results as seen in the FIT pilot study, another 1-2 CRC cases are likely to be undiagnosed in FIT negative (false negative) individuals. Therefore, if we assume a worst case occurrence of 2 false negative cases (i.e., 2 cancers in the 3686 FIT negative tests), then we can estimate that 3933 (total n of “prevalent first-time invitees”)-6-2 = 3925 individuals are without CRC of whom 3686 – 2 = 3684 have FIT negative results, leading to an estimated specificity of 94% (3684 / 3925) in the patient population for this ‘FIT for Lynch Study’.

Assuming approximately three quarters of the eligible 2745 LS patients are due for colonoscopy within the 18 month recruitment period (2745 × 0.75 = 2059), and in considering the projected response/uptake rate of ~ 63%, (which has since been observed in the same patient population as part of the continuing NHS England clinical service evaluation [18]), it is estimated that 1297 individuals will return a FIT sampling kit.

On aiming to recruit 400 Lynch Syndrome patients on surveillance (when considering existing available funding), we anticipate 352 (88%), will not have detectable advanced neoplasia and will be used to evaluate the specificity. Assuming true specificity of 94%, then the width of a 95% confidence interval will be approximately 5%. These numbers would also provide 87% power to show that the specificity is at least 90%. This is based on a one-sided one-sample score test of proportions with a 5% significance level using STATA/SE v. 17.0.

We will employ a modified intention-to-treat (mITT) approach whereby participants who return at least 1 FIT kit and have an outcome from colonoscopy are available for analysis. Participants whose colonoscopy result is unavailable are likely to be relatively uncommon when considering the high rate of colonoscopy surveillance adherence in this patient population [19, 20]. Nonetheless, we will report the frequency of those without colonoscopy and the frequencies of those returning 0, 1 or 2 FIT kits.

### Study population: inclusion and exclusion criteria

Inclusion criteria: Patients will have a confirmed pathogenic variant in any four MMR genes (*MLH1, MSH2, MSH6, PMS2),* or have a confirmed pathogenic variant in *EPCAM.* For those with pathogenic variants in *MLH1* or *MSH2,* the age requirements for eligibility will be between 25 and 73 years, and for patients with pathogenic variants in *PMS2, MSH2* or *EPCAM* must be between the ages of 35 – 73 years of age. Eligible patients must also have an upcoming (within the year of active recruitment) standard of care (SOC) colonoscopy appointment at any NHS Trust. Age criteria is defined by gene-specific colonoscopy eligibility, with the upper maximum age limit in this instance defined by the upper age limit for LS surveillance guidelines (75 years of age) [5], with 2 years subtracted to accommodate a surveillance SOC colonoscopy at Study Year 2.

Exclusion criteria: Individuals who have previously undergone a subtotal or total colectomy and/or those who are unable to provide consent in English will be excluded from this study.

### Baseline recruitment

Potential eligible participants will be identified by the local PI and study team of the respective participating NHS Trusts via a i) Lynch Syndrome registry ii) local regional genetics service databases iii) through linked endoscopy clinical records held within their local Regional NHS Trusts and/or iv) through the completion of a reply slip that may be sent from a participating Regional Genetics Service (study site) direct to their LS patients, which shall be sent along with a patient inquiry letter as part of an initial optional patient mailing, as detailed below. Inclusion and exclusion criteria will be verified by the hospital clinical records. Ethically-approved advertisement flyers and patient informational posters will be shared amongst Lynch Syndrome support groups and related networks as an addition strategy to inform eligible patients about the study.

The Research laboratory at the Bowel Cancer Screening South of England Hub (referred to as the “Southern Hub laboratory”), based at the Royal Surrey County NHS Foundation Trust in Guildford, will act as the central laboratory for this study. Participating study sites will email an excel spreadsheet containing patient details by secure nhs.net email patients meeting full inclusion criteria for the study. Southern Hub laboratory research staff will compile baseline mailings (Year 0) for each eligible patient which will be mailed direct to eligible patients within 7-30 days prior to their next scheduled standard of care (SOC) colonoscopy. This specific time frame (7-30 days) was devised by considering FIT kits to be received by eligible patients prior to commencing bowel preparations for colonoscopy, and in considering potential mail delays or delivery disruptions.

Prior to the distribution of a baseline mailing, Southern Hub laboratory research staff will assign a Study ID to each eligible patient which will be recorded within a secure master database internal to the Southern Hub research laboratory and restricted solely to assigned study staff.

The baseline mailings will comprise a i) study invitation letter ii) a faecal immunochemical test (FIT) kit (OC-Sensor™, Eiken Chemical Co. Ltd., Tokyo, Japan) enclosed within a biospecimen sample bag iii) a consent form, which will include an opt-in to allow for additional research as part of the exploratory aim to examine the faecal microbiome of LS patients, iv) pictorial and written instructions for collection of the faecal sample (FIT instruction sheet), v) a participant questionnaire, vi) a participant information sheet (PIS), and vii) a return envelope with prepaid postage for return to the Southern Hub.

For any participating Regional Genetics Services (study sites) who are unable to access requisite colonoscopy appointment details for their LS patients, an optional patient inquiry letter and accompanying reply slip may be mailed directly from said study sites to their LS patients who have met all preceding eligibility criteria.

Consent to this study will be implicit upon return of a completed FIT kit at Baseline (Year 0), though all participants are free to withdraw at any time. Any study data and/or relevant (pseudo-anonymised) clinical data that has been collected until this point, however, will remain as part of the study database and therefore retained by the study team.

Upon receipt of any study FIT kits (Baseline + Years 1-3), a numerical sample ID, which will be consistent with the accompanying barcode found on each FIT kit label, will be assigned and linked to the participant’s previously assigned study ID. Each returned FIT kit will be analysed on one of two OC-Sensor™ Pledia analysers within 14 days of sample collection.

F-Hb results will be reported down to the limit of detection (LoD) (1 μg/g f-Hb), as recommended by Fraser and Benton [15, 21, 22].

Pseudo-anonymised data, including Study ID’s, relevant demographic variables, and f-Hb concentration results of study participants, will be recorded by assigned Southern Hub laboratory research staff within respective electronic clinical report forms (eCRF’s) as part of the FIT for Lynch Study database. This study database will use REDCap electronic data capture tools hosted by the coordinating centre, King’s College London (KCL) [23, 24].

### Post-baseline study years 1-3: contact & mailings

Following active recruitment and baseline period (Year 0), participants will be re-contacted by Southern Hub laboratory research staff via mail on an annual basis for an additional 3 years (Study Years 1-3) after baseline (Year 0). Subsequent mailings for enrolled participants for Years 1-3 will be comprised of the following items and materials: i) a participant post-baseline letter, ii) a participant information sheet, iii) an OC-Sensor™ FIT kit enclosed within a biospecimen bag, iv) a FIT instruction sheet, and a v) return envelope with prepaid postage. Mailing of study materials and FIT kits for study participants at Study Year 2 will be sent ahead of their SOC colonoscopy at this time point (in line with the UK’s LS surveillance guidelines) also within a 7–30-day window (See Fig. 1 and Table 1) .

**Fig. 1 Fig1:**
[figure not shown]
FIT for Lynch Study Schematic. *** =** Per the inclusion criteria, eligible patients with *MLH1* OR *MSH2* pathogenic variants must be between 25 and 73 years of age, whereas eligible patients with pathogenic variants in *PMS2, MSH6,* or *EPCAM* must be between 35 and 73 years of age

**Table 1 Tab1:** Study schedule of events (baseline & years 1-3)

Study Participants (SP)	Active Recruitment (initial 12 months post study start)	Screening (7-30 days prior to colonoscopy)	Baseline (7-30 days prior to colonoscopy)	1-year post-baseline	2-years post-baseline	3-years post-baseline
Eligibility assessment		x				
^α^ Patient Inquiry Letter and reply slip	x					
FIT Kit, FIT instruction sheet, patient letter, patient information sheet (mailed)			x	x	x	x
Study invitation letter, consent form, baseline questionnaire, patient information sheet			x			
Post-baseline letter				x	x	x
^‡^Follow-up Questionnaire						x
SOC colonoscopy			+		+	
**Colonoscopy referred via 2WW				**+		**+

x Research related procedure.

+ SOC procedure (as per recommended guidelines)

α Optional mailing for study sites who may not have access to requisite colonoscopy appointment data (direct mailing between said study sites and LS patients).

^**‡**^ A follow-up questionnaire to assess evolving perceptions and attitudes towards FIT is presently under development as of the time of this writing and will be forthcoming for inclusion within the study design ahead of its planned distribution to study participants at Year 3

** Enrolled patients shall be referred for a colonoscopy (by their consultant) via the two-week wait (2WW) pathway performed at intervening years between SOC biennial colonoscopy (Years 1 &3) *only* in the event their FIT result ≥6 μg/g f-Hb

Returned FIT kits in post-baseline Study Years 1-3 will follow the same standard operating procedure for analysis and eCRF reporting as detailed above for baseline mailings and study samples.

### FIT kit results Reporting & Urgent Colonoscopy Triage for eligible study participants (SP) at study years 1 & 3

F-Hb results to come from this study will not be directly disclosed to participants. Site Principal Investigator’s (PI’s) will receive electronic reports of f-Hb results if ≥6 μg/g study participants’ directly from the Southern Hub laboratory via NHS secure and encrypted emails in Years 1 and 3 (the intervening years between a study participant’s SOC colonoscopy) to inform triage for colonoscopy. FIT positivity in study participants will be determined by the limit of quantification (LoQ) at the pre-determined threshold of ≥6 μg/g f-Hb [22].

Although it is anticipated that only a small minority of study participants may meet criteria for an additional interval colonoscopy at Years 1 & 3 (approximately 10%, based on early data as part of a preceding emergency clinical service evaluation), those that are identified as “FIT positive” at the specified study periods will be contacted by their respective local PI to discuss their FIT results and advised to proceed with a colonoscopy which will be triaged via the NHS’ urgent two-week-wait (2WW) referral pathway.

Throughout the duration of the study, endoscopy and pathology reports will be securely sent from respective study sites to the coordinating centre for the abstraction of relevant outcome data which will be stored and managed within the FIT for Lynch REDCap database.

### Compliance

To ensure a high adherence to the trial protocol and the completion of annual FIT kits, eligible patients receive clear FIT kit instructions, as well as detailed study materials and the FIT kit on an annual basis throughout the course of the study (Fig. 1). For post-baseline periods (Years 1-3), participants receive a personalised post-baseline letter which serves as a reminder of their study participation and to request the timely return of their FIT kit at the specified study point. For baseline (Year 0) and Year 2, participants are encouraged to return their FIT kit to the Southern Hub ahead of their scheduled SOC colonoscopy and prior to beginning their bowel prep by utilising an enclosed pre-paid envelope which allows for simplicity, ease, and a cost-free method in delivering study samples.

### Data collection and planned analysis

Colonoscopy and/or histopathology reports will be requested for all participating individuals who return a FIT kit throughout the duration of the trial (Baseline + Years 1-3) as part of the outcome data required for analysis. After the trial has ended, and dependent on the procurement of additional research funds, we will continue to passively observe a subset of trial participants who had preceding negative FIT results to discern potential incidence of interval advanced colorectal neoplasia (ACN) over the course of 3 years. The study has received written approval from the Research Ethics Committee (REC) of Clinical Research of each participating region (REC Reference: 21/YH/0066).

A secure and encrypted database will be constructed with a unique study ID for each participant and routinely checked for errors. A summary of study variables to be collected are reflected within Table 2.

**Table 2 Tab2:** Study measurements

Participant	
Study ID, DOB^a^, sex, ethnicity, NHS Lynch Syndrome genotype, local PI and participating NHS Trust.	
FIT Data	
Dates of participant mailings sent from the Southern Hub (baseline and years 1-3), FIT results (f-Hb for baseline and years 1-3.	
Clinical^a^	
Date of colonoscopy at baseline and years 1-3 + follow-up years 4-6 for the subset of eligible patients, histological features and staging (where applicable) of biopsied specimen(s) at time of colonoscopy, anastomosis (Y/N), gastrointestinal (GI) comorbidities (Y/N), History of CRC (Y/N), date of CRC (where applicable), prior GI surgery (Y/N), GI surgery type (where applicable), other cancer(s) (Y/N), bowel prep quality, polyp retrieval (Y/N), colonoscopy key performance indicators (KPI) met (Y/N), aspirin use (Y/N), aspirin dosage (where applicable), additional medications (Y/N), additional medication details and dosage (where applicable).	

^a^Data to be collected only for those who return a sample i.e., consent

Both interim and final datasets will be created and analysed within Stata statistical software. The REDCap database and related .csv files will be imported into Stata for final cleaning and analysis.

The interim dataset will be developed and analysed within Stata by the Project Manager and PhD student, [name], as part of her PhD thesis. The preliminary data will be comprised of all available baseline data (e.g., FIT results, baseline questionnaire responses, and endoscopy and histopathology results (where applicable) for SOC colonoscopies at baseline)).

Additional data will be collected from participant questionnaires included in the baseline mailing to address the secondary study objective.

### Outcomes and endpoints

A detailed description of the objectives and the measurement of study outcomes is provided herein (see Table 3).

**Table 3 Tab3:** Measurement timepoints of study objectives

*Study Objectives*		*Measurement Timepoints*				
*Objective Type*	*Objective Summary*	*Baseline (Y0)*	*Y1*	*Y2*	*Y3*	*Passive Follow-Up (Y4-Y7)*
Objective 1 (Primary)	To evaluate the specificity of FIT for the detection of CRC and AA’s in patients with LS.	x	x	x	x	
Objective 2 (Secondary a)	To identify and explore acceptability, views, and preferences of FIT in this patient population	x				
Objective 3 (Secondary b)	To evaluate the sensitivity of FIT for the detection of CRC in patients with LS	x	x	x	x	
Objective 4 (Secondary c)	To evaluate the sensitivity of FIT for the detection of AA’s in patients with LS	x	x	x	x	
Objective 5 (Exploratory)	To examine and characterise the faecal microbiome of patients with LS.	x	x	x	x	
Objective 6 (Exploratory)	To observe the incidence of interval CRCs for LS patients with FIT negative results (< 6 μg/g f-Hb)					x^a^

^a^*This outcome will be measured in a subset of study participants*

### Primary outcomes

#### Objective 1 (primary)

Primary outcomes are evaluated at all time points (Baseline (Y0) + Years 1-3 (Y1-Y3)) and will entail the assessment of true negative and false negative rates in this participant cohort to observe ≥90% specificity. In this context, true negative is defined as having no visible CRC or AA’s at time of colonoscopy and a subsequent normal or “negative” endoscopy and/or pathology report for participants with preceding FIT negative (< 6 μg/g f-Hb) results.

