#### Objective 3 (secondary objective (b))

Secondary outcomes for secondary objective (b) are evaluated at all time points (Y0 – Y3) and will entail the assessment of true positive and false negative rates in this participant cohort to observe > 87% sensitivity. True positive (TP) cases are defined as the confirmation in the detection of colorectal neoplasia at time of colonoscopy for patients with preceding positive FIT results (≥6 μg/g f-Hb) and will be evaluated at thresholds of 6, 10 and 100 μg/g for patients meeting this criteria of TP.

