#### Objective 4 (secondary objective (c))

Secondary outcomes for secondary objective (c) are evaluated at all time points (Y0 – Y3) and will entail the assessment of true positive and false negative rates in this participant cohort to observe > 87% sensitivity. True positive cases in this context are defined as the confirmation in the detection of AA’s alone at time of colonoscopy for patients with preceding positive FIT results (≥6 μg/g f-Hb) and will be evaluated at thresholds of 6, 10 and 100 μg/g for patients meeting this criteria of TP.

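### Specificity and sensitivity are set for all four rounds, but at Years 1 and 3 only FIT-positive participants are referred for colonoscopy, so FIT-negatives there have no same-round reference standard

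*Protocol article*

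**What the plan says.** **Time points for accuracy.** Under Objective 1 (primary), with a specificity target of at least 90%: "Primary outcomes are evaluated at all time points (Baseline (Y0) + Years 1-3 (Y1-Y3". Under Objective 3, with a sensitivity target above 87%: "Secondary outcomes for secondary objective (b) are evaluated at all time points (Y0 – Y3". Under Objective 4, with the same target: "Secondary outcomes for secondary objective (c) are evaluated at all time points (Y0 – Y3". Table 3 marks Y0, Y1, Y2 and Y3 for all three objectives.

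**Who has a colonoscopy, and when.** Table 1 places standard-of-care colonoscopy at baseline and Year 2. Its footnote says that the additional colonoscopy is "performed at intervening years between SOC biennial colonoscopy (Years 1 &3) *only* in the event their FIT result" reaches 6 μg/g. The section on results reporting and triage agrees, calling Years 1 and 3 "the intervening years between a study participant’s SOC colonoscopy".

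**What counts as a true negative.** Objective 1 requires a negative FIT and a colonoscopy showing no cancer or advanced adenoma.

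**Analysis set.** Under Study design, "participants who return at least 1 FIT kit and have an outcome from colonoscopy are available for analysis". Nothing there ties a FIT result to a colonoscopy in the same round.

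**Sample size.** Study design counts 352 participants without advanced neoplasia (88% of 400), once each, with assumed true specificity 94%.

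**The concern.** The accuracy objectives cover two rounds in which verification depends on the test result itself. At Years 1 and 3 a positive FIT leads to colonoscopy and a negative one does not. The cells for true negatives and false negatives are then empty by design, while those for true and false positives fill up. This is partial verification.

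The article gives no rule for the FIT-negatives of Years 1 and 3: no delayed reference, no correction, and no statement of which round or rounds carry the 90% target. An analyst who follows the text and uses every FIT with a same-round colonoscopy would lower specificity and raise sensitivity. The primary result could miss its target when the test meets it, and the sensitivity result could meet its target when the test does not.

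**Working it through.** **Inputs from the article (Study design, unless noted):** 352 participants without advanced neoplasia; true specificity 94%; null value 90%; one-sided 5% score test; stated power 87% and 95% confidence interval width about 5%; FIT positivity at Years 1 and 3 about 10% (triage section).

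**Assumptions of this check:** 352 disease-free participants in each round; every positive at Years 1 and 3 has a colonoscopy; return in Years 1-3 of 100%, 80% or 63%. The last is the article's projected baseline uptake, borrowed here for follow-up.

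1. **The plan's own figures.** Power = Φ{[(0.94 − 0.90) − 1.645·√(0.90·0.10/352)] / √(0.94·0.06/352)} = 0.860, close to the stated 87%. Interval width = 2·1.96·√(0.94·0.06/352) = 0.0496. Both reproduce, so the sample size fits one fully verified test per participant.

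2. **Counts per round.** True negatives 352·0.94 = 330.9; false positives 352·0.06 = 21.1.

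3. **Year 1 or Year 3 alone, same-round verification.** True negatives and false negatives are both zero by design. The ratios would be 0% specificity and 100% sensitivity whatever the truth. This shows the logic; it does not forecast a reported result.

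4. **Four rounds combined, full return.** True negatives arise only at Y0 and Y2: 2·330.88 = 661.8. False positives arise in all four rounds: 4·21.12 = 84.5. Specificity = 661.8/(661.8 + 84.5) = 88.7%. Y0 and Y2 alone give 94%.

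5. **Lower return r in Years 1-3.** Specificity = 330.88·(1 + r) / [330.88·(1 + r) + 21.12·(1 + 3r)].
   - r = 0.80: 595.6/667.4 = 89.2%.
   - r = 0.63: 539.3/600.4 = 89.8%.

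6. **Using the article's 10% positivity instead.** That is 40 referrals per round from 400. If 50% of them are free of advanced neoplasia (assumed): 661.8/(704 + 40) = 88.9%. If 100%: 661.8/(704 + 80) = 84.4%.

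7. **Dependence on the true value.** With full return, pooled specificity = s/(2 − s). It reaches 90% only when s = 1.8/1.9 = 94.7%. At s = 96% it is 0.96/1.04 = 92.3%.

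8. **Delayed reference for Year 1.** Suppose Year 1 negatives were verified at the Year 2 colonoscopy and Year 3 negatives stayed unverified. True negatives = 3·330.88 = 992.6, and specificity = 992.6/(992.6 + 84.5) = 92.2%. This is above 90% but still below the true 94%.

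9. **Sensitivity.** Let S be true sensitivity and w the number of cases at Years 1 and 3 relative to Y0 and Y2. Apparent sensitivity = (2S + 2wS)/[2S + 2wS + 2(1 − S)]. Take S = 82.2%, a literature value that the article cites for cancer at a 20 μg/g threshold, used only as an illustration.
   - w = 1: 90.2%.
   - w = 0.5: 87.4%.
   - w = 0.25: 85.2%.

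   The first two pass the 87% target although the true value does not.

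**The case against.** **Pooling is not stated.** A reader might infer that the plan pools the four rounds and that the primary result is therefore certainly biased. The article does not say so. Evaluation at each time point could mean round-by-round reporting, and the only stated unit is the participant. This stands, and the bias in the primary result is conditional on combining rounds. It does not remove the problem, because separate estimates at Years 1 and 3 are not obtainable from same-round verification either.

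**A later colonoscopy could serve as reference.** A reader might infer that accuracy at Years 1 and 3 can never be estimated. That is too absolute. The true-negative definition speaks of a preceding negative FIT, and everyone is due a colonoscopy at Year 2. A Year 1 negative could be verified there, about a year late, and the figure would then be 92.2%. But the article does not state this rule, positives and negatives would be verified at different delays, and Year 3 has no assured counterpart. Table 2 does foresee colonoscopy dates in later years, but that follow-up is passive, in a subset and dependent on funding.

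**Other stronger readings.** Two further criticisms are tempting, and the article does not support them:
- That the score test is invalid for repeated tests. The article names that test only in the power calculation, with 352 people counted once. Handling of repeats is ordinary analysis-plan content.
- That Year 2 is biased because lesions found at Year 1 have been removed. No figure supports a size for this, and it would concern the case mix for sensitivity, not the primary specificity.

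**An analysis plan may settle it.** It may, but the time points are fixed in this article, so a plan that dropped Years 1 and 3 would contradict the primary outcome and Table 3.

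**Conclusion.** The contradiction lies within the article. Objectives 1, 3 and 4 and Table 3 require accuracy at Years 1 and 3, while Table 1 and the triage section withhold the same-round reference from FIT-negatives in those years.

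If rounds are combined on same-round verification, a true specificity of 94% appears as 88.7% to 89.8% over the assumed return range, below the 90% target. With 10% positivity it appears as 84.4% to 88.9%. A true sensitivity of 82.2% appears as about 87% to 90% when Years 1 and 3 hold half as many to equally many cases, and as 85% when they hold a quarter.

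These sizes rest on the stated assumptions. The shortfall at 63% return is only 0.2 points, and a true specificity of 96% would still pass with full return. The direction of the bias does not depend on those choices. The sample size is not in error. It matches a single, fully verified round.

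**What to change.** State that the 90% specificity test and both sensitivity objectives rest on rounds in which all participants are due a colonoscopy. Either option cures the defect:

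- **Y0 alone:** baseline FIT paired with the baseline colonoscopy, one test per participant, as the 352 already assumes, with Year 2 as a secondary replicate.
- **Y0 and Y2 together:** with clustering by participant taken into account.

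At Years 1 and 3 report FIT positivity, positive predictive value and colonoscopy yield only. Amend the Y1 and Y3 marks for Objectives 1, 3 and 4 in Table 3, and the wording on time points under those three objectives. The referral rule and the schedule of procedures stay as they are. The planned interim analysis of baseline data need not become the single primary test; that is the sponsor's choice, provided that the round or rounds carrying the 90% test are named.

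The cost is wording. The study gives up accuracy claims at Years 1 and 3, and under the Y0-only option the Year 2 cases move to a secondary analysis, which matters most for sensitivity.

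### The primary specificity outcome pairs true negatives with false negatives instead of false positives, and its 90% target is not reconciled with the powered score test

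*Protocol article*

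**What the plan says.** The primary outcome, under Objective 1 (primary), "will entail the assessment of true negative and false negative rates in this participant cohort to observe ≥90% specificity". It is to be evaluated at baseline and Years 1 to 3. A true negative is then defined as no CRC or advanced adenoma at colonoscopy, with a normal report, "for participants with preceding FIT negative (< 6 μg/g f-Hb) results". The matching entry in the Objectives section also describes only FIT-negative participants. No objective or outcome defines a false positive; the term appears only where limitations are discussed.

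The sensitivity outcome under Objective 3 uses the same sentence pattern: "the assessment of true positive and false negative rates in this participant cohort to observe" a stated sensitivity. Objective 4 repeats it. There the two cells named, true positive and false negative, are the right ones.

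The Study design section handles specificity differently. It derives the planning value as FIT negatives among people without CRC (3684/3925, or 94%) and says of the 400 recruits: "we anticipate 352 (88%), will not have detectable advanced neoplasia and will be used to evaluate the specificity". On the criterion it says "These numbers would also provide 87% power to show that the specificity is at least 90" per cent, based on a "one-sided one-sample score test of proportions with a 5% significance level".

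**The concern.** Specificity is TN/(TN+FP), taken over people without the target disease. False negatives are people with the disease, so they belong to sensitivity and to NPV. If the Objective 1 sentence is read as its counterparts in Objectives 3 and 4 must be read, as the two cells of the ratio, it gives TN/(TN+FN), which is NPV. When most participants are disease-free, NPV is high almost regardless of specificity. Specificity is also what determines how many participants have an unnecessary extra colonoscopy, which the Discussion names as a possible harm.

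The target raises a second question. Reaching an observed 90% and rejecting a null value of 90% are different hurdles, and the article does not say which one Objective 1 means.

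**Working it through.** **Inputs.** From Study design: 400 recruits, 352 (88%) without advanced neoplasia, hence 48 (12%) with it; null specificity 0.90; true specificity 0.94; one-sided 5% score test; stated power 87%. From Objectives 3 and 4: sensitivity target above 87%. Sensitivities of 50% and 30% are assumptions for illustration; the article gives no expected value for advanced neoplasia in this population. One FIT result per participant is assumed, which is how the 352 is counted.

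**1. The plan's own figures.**
- Standard error at the null: √(0.90×0.10/352) = 0.01599. At the alternative: √(0.94×0.06/352) = 0.01266.
- Power = Φ[(0.04 − 1.645×0.01599)/0.01266] = Φ(1.08) = 86.0%, against 87% stated.
- 95% interval width: 2×1.96×0.01266 = 0.0496, against about 5% stated.

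Both agree, so the sizing is for specificity among disease-free participants, tested by the score test.

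**2. Which quantity the named cells give.**
- Specificity at planning values: TN = 352×0.94 = 330.9 and FP = 21.1, so TN/(TN+FP) = 94%.
- TN/(TN+FN) = 352×sp / [352×sp + 48×(1−se)], where sp is specificity and se is sensitivity.
- sp 0.80, se 0.50 (assumed): 281.6/(281.6+24) = 92.1%.
- sp 0.60, se 0.87 (the target value): 211.2/(211.2+6.24) = 97.1%.
- Setting the ratio to 0.90 gives sp = 9×0.12×(1−se)/0.88, which is 61% at se 0.50 and 86% at se 0.30. Above those values the ratio passes 90% whatever the specificity.

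**3. Observed 90% against the score test, n = 352.**
- Observed 90%: 0.90×352 = 316.8, so 317 negatives are needed.
- Score test: 0.90 + 1.645×0.01599 = 0.9263; ×352 = 326.06, so 327 are needed (92.9%). Exact binomial type I error is 3.8% and exact power 83.8%.
- Probability of 317 or more: 53.1% if true specificity is 90%, 29.7% if 89%, 99.9% if 94%.
- Probability of landing between 317 and 326: 53.1% − 3.8% = 49.3% at a true 90%, and 99.9% − 83.8% = 16.1% at a true 94%.

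**4. Rounds in which the ratio can be formed.** Table 1 schedules standard-of-care colonoscopy at baseline and Year 2. At Years 1 and 3 a study colonoscopy follows only a FIT of 6 μg/g or more. A specificity based on paired colonoscopy in those two years would contain false positives but essentially no true negatives, although Objective 1 and Table 3 list all four time points.

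**The case against.** The strongest reply is that the article fixes the estimand as specificity everywhere: in the Objectives, in Table 3, in the Study design section and in the disputed sentence itself. NPV is never mentioned. The sentence speaks of rates, and the true negative rate is simply another name for specificity, so one wrong word has slipped in beside it. FIT positivity and the disease-free state are both defined, so a reader can work out the false-positive cell. The verb *observe* is used loosely throughout, and the only inferential criterion stated is the score test.

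Much of this stands. A reader might infer that the primary analysis will be an NPV, or that the plan has adopted a point-estimate rule with a 53% error rate. The documents support neither: the denominator is given correctly in Study design, and Objective 1 states no decision rule. The NPV and error figures above show what the literal wording would allow, not what the authors have said they will do.

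What does not fall away is that the primary endpoint text names a quantity that plays no part in specificity, leaves out the one that does, and carries a 90% target that is not linked to the test. These are errors in what the article states. They are not details left to an analysis plan.

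**Conclusion.** The concern holds as an error and an unresolved inconsistency in the primary endpoint text. The second cell should be false positives, as the article's own denominator shows. Read literally as a pair of cells, the text gives a quantity that can exceed 90% with poor specificity: 92% at 80% specificity, given 12% advanced neoplasia and an assumed sensitivity of 50%. On the target, 317 to 326 negatives out of 352 would satisfy Objective 1 as worded and fail the Study design test. These counts assume exactly 352 disease-free participants with one result each, and would shift with the number achieved. The stated power and interval width reproduce to within rounding or one percentage point, and neither they nor the sample size needs to change.

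**What to change.** Rewrite the Objective 1 outcome so that it:

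- replaces the false negative rate with the false positive rate;
- defines a false positive as FIT of 6 μg/g or more with no CRC or advanced adenoma at the paired colonoscopy;
- states specificity as TN/(TN+FP) among participants without CRC or advanced adenoma;
- ties the 90% criterion to the one-sided 5% score test in Study design, or to the matching lower confidence bound;
- bases the primary estimate on baseline and Year 2, where colonoscopy is scheduled whatever the FIT result, and says how two results from one participant are handled, since the 352 counts participants;
- reports NPV separately, under its own name.

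Align the Objectives entry and the Table 3 time points with this. The cost is a paragraph of wording and a table edit, with no new data and no change in sample size. It should be done before the primary analysis.
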